### 8.3.3 Subject withdrawal

Subjects may withdraw from the protocol at any time. Subjects may withdraw permission for the use of unprocessed specimens, at which time those samples will be destroyed. This request must be made in writing, addressed to the PI. Data regarding DNA sequences will be unable to be destroyed at the request of the subject. Any sample, portion of a sample or product derived from that sample that has already been used in research, will not be able to be retrieved and destroyed.

## 8.4 Criteria for Study Suspension

8.4.1 The study will be suspended if there is any death within four weeks after the first dose of IFN- $\gamma$ , which is probably or definitely attributed to IFN- $\gamma$ , by the treating physician, site PI or study PI. IRB review would follow. Subjects already on IFN- $\gamma$  would stop their injections.

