**Figure 4. The dose adjustment plan for IFN- $\gamma$  for cohort 1.**

- Schedule of IFN- $\gamma$  and dose adjustment for cohort 2 (Figure 5)
- 1) The initial dose of IFN- $\gamma$
- a. The first dose of IFN- $\gamma$  100 mcg will be administered on day 0 in the clinic.
  - b. The subject will continue self-injection of 100mcg, three times a week for two weeks (e.g., Monday, Wednesday, Friday or Tuesday, Thursday, Saturday)

- 2) 48 hours after the initial dose of IFN- $\gamma$  (up to 1 week)
  - a. Bone marrow aspirate (no biopsy) will be performed for morphology, flow cytometry, and a research sample. (Cytogenetics/molecular testing only needed if clinically indicated to follow MRD.)
- 3) One week after the initial dose of IFN- $\gamma$  (window: - 3 days to + 7 days)
  - a. Subjects tolerating 100 mcg three times a week can proceed to DLI if eligible.
  - b. If the subject is not tolerating a given dose, it can be decreased to 100mcg two times a week for one week (+/- 5 days). If tolerated, the patient would then be eligible to proceed to the DLI phase.
  - c. If 100 mcg two times per week is not tolerated, IFN- $\gamma$  will be discontinued, and the subject will be withdrawn from further on-study treatment. The subject may still proceed to DLI off study.

[figure not shown]

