#### 6.4.2.2 For the subjects for whom donor leukocytes are available (cohort 2)

- After the first dose of DLI, the same dose of IFN- $\gamma$  as used pre-DLI for that patient will be continued three times a week for four weeks. If the subject develops intolerance to IFN- $\gamma$  during this period, we will reduce the frequency of IFN- $\gamma$  to once weekly.
- A minimum of four weeks after the first dose of DLI, the subject will receive the second DLI, in the absence of active grade II-IV GVHD or de novo grade III-IV, or progressive chronic GVHD requiring new systemic treatment or increased doses of current systemic treatment per treating physician's determination. IFN- $\gamma$  will be continued at the same dose three times weekly. There is an optional bone marrow aspirate if clinically indicated prior to the second DLI per the treating physician, and a research sample can be collected at that time.
- 8 weeks after the first dose of IFN- $\gamma$  (or approximately 7 weeks after the first dose of DLI), the frequency of IFN- $\gamma$  will be tapered to once weekly, continued until the next DLI.
- A minimum of 4 weeks after the second DLI, the subject will receive the third dose of DLI, in the absence of active grade II-IV GVHD or de novo grade III-IV, or progressive chronic GVHD defined by a requirement for new systemic treatment or increased doses of current systemic treatment. IFN- $\gamma$  will be continued at the same dose once weekly for three more weeks. There is an optional bone marrow aspirate if clinically indicated before the third DLI, and a research sample may also be collected at that time.
- IFN- $\gamma$  will be continued once weekly until four weeks of the last dose of DLI or 12 weeks after the first dose of IFN- $\gamma$  whichever occurs later. If the subject develops intolerance to IFN- $\gamma$  during this period, we will discontinue IFN- $\gamma$
- At the end IFN- $\gamma$  treatment, the bone marrow aspirate is required ideally within seven days after the last dose of IFN- $\gamma$

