#### 6.5.2.2 Protocol visit #1: Stage 1, the first dose of IFN- $\gamma$

- Pre-treatment assessment (bone marrow aspirates, vital signs, and clinical assessment) as described in 6.3.1 will be performed before IFN- $\gamma$  administration.
- **Bone marrow aspirates** (no biopsy) will be performed for morphology, flow cytometry, and research sample (10mL) if the bone marrow research sample is not collected within two weeks before the first dose of IFN- $\gamma$ .
- Research sample collection: A bone marrow aspirate with a goal of 10 mL collected (in 10ml green top heparin tube x 1) and 30 mL of peripheral blood (10 mL green top heparin tube x 3 tubes) will be obtained as a baseline sample before IFN- $\gamma$  administration.
- First dose of IFN- $\gamma$  will be administered after the safety assessment.
- As described in 6.3.1., the patient will receive the training for self-injection of IFN- $\gamma$
- Safety monitoring: Subjects will be assessed for an acute reaction to the IFN- $\gamma$  or complication of biospecimen collection. Subjects will stay in the clinic for at least 1 hour after IFN- $\gamma$  administration and be assessed by a physician, physician assistant, advanced practice nurse or nurse prior to discharge from the clinic.

6.5.2.3 Protocol visit #2: Stage 1, minimally 48 hours (up to one week) after the first dose of IFN- $\gamma$ : Safety and biological assessment of IFN- $\gamma$ , bone marrow aspiration for research

- Clinical safety monitoring: Any reaction or symptoms related to the prior doses of IFN- $\gamma$  and will be assessed specifically focusing on active grade II-IV GVHD or de novo grade III-IV, or progressive chronic GVHD
- **Bone marrow aspirates** (no biopsy) will be performed for morphology, flow cytometry, and research sample (10mL).
- Research sample collection: 10mL of bone marrow (10ml green top heparin tube), 30 mL of peripheral blood (10 mL green top heparin tube x 3 tubes) will be collected.
- The subsequent doses of IFN- $\gamma$  will be administered after the safety assessment.

6.5.2.4 Protocol visit #3: End of stage 1 and pre-treatment evaluation for stage 2 (donor lymphocyte infusion), Day +7 (-3 days to +5 days) after the first dose of IFN- $\gamma$ : Safety assessment of IFN- $\gamma$

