- Clinical safety monitoring: Any reaction or symptoms related to the prior doses of IFN- $\gamma$  and will be assessed specifically focusing on active grade II-IV GVHD or de novo grade III-IV, or progressive chronic GVHD
- Laboratory monitoring: CBC with differential, chemistry panel (Na, K, Cl, CO2, creatinine, glucose, urea nitrogen, phosphorus, magnesium, albumin, calcium, LDH, uric acid), hepatic (alkaline phosphatase, ALT, AST, and total bilirubin) panel
- The subsequent doses of IFN- $\gamma$  will be administered after the safety assessment.
- If DLI is available, the first dose of DLI will be infused within two weeks from this visit.

6.5.2.5 Protocol visit #4: Stage 2 first safety assessment, 21 days (+/- 5 days) after the first dose of IFN- $\gamma$ , or 14 days (+/- 5 days) after the first dose of DLI.

- Clinical safety monitoring: Any reaction or symptoms related to the IFN- $\gamma$  or DLI will be assessed, specifically focusing on active grade II-IV GVHD or de novo grade III-IV, or progressive chronic GVHD
- Laboratory monitoring: CBC with differential, chemistry panel (Na, K, Cl, CO2, creatinine, glucose, urea nitrogen, phosphorus, magnesium, albumin, calcium, LDH, uric acid), hepatic (alkaline phosphatase, ALT, AST, and total bilirubin) panel
- The subsequent frequency IFN- $\gamma$  will be reduced to once-weekly dosing for four more weeks.

6.5.2.6 Protocol visit #5: Stage 2 follow up safety assessment, 35 days (+/- 5 days) after the first dose of IFN- $\gamma$ , or 28 days (+/- 5 days) after the first dose of DLI

- Clinical safety monitoring: Any reaction or symptoms related to the IFN- $\gamma$  or DLI will be assessed, specifically focusing on active grade II-IV GVHD or de novo grade III-IV, or progressive chronic GVHD
- Laboratory monitoring: CBC with differential, chemistry panel (Na, K, Cl, CO2, creatinine, glucose, urea nitrogen, phosphorus, magnesium, albumin, calcium, LDH, uric acid), hepatic (alkaline phosphatase, ALT, AST, and total bilirubin) panel
- STR chimerism of bone marrow (if collected) and peripheral blood (whole blood, or CD3 and myeloid)
- Research sample collection: 30 mL of peripheral blood (10 mL green top heparin tube x

3 tubes) will be collected.

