## **8. STATISTICAL CONSIDERATIONS**

### **8.1 Study Endpoint**

#### **8.1.1 Primary safety endpoint:**

To evaluate the adverse events of IFN-γ in relapsed patients after alloSCT, per CTCAE v5.0

To evaluate the adverse events of IFN-γ in relapsed patients after alloSCT with concurrent use of donor lymphocyte infusion, per CTCAE v5.0

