### 8.4.2 Criteria for study resumption after a safety pause

The IFN- $\gamma$  injection and enrollments of new subjects would resume only if a review of the adverse events that caused the pause resulted in an IRB recommendation to permit further study injections and study enrollments.

The Principal Investigator will consult with the IRB to conduct the review and make the decision to resume or close the study for any SAEs that meet the criteria for pausing the study. As part of the pause review, the reviewers will also advise on whether the study needs to be paused again for any subsequent adverse events of the same type. When indicated, safety data reports and changes in study status will be submitted to the IRB and FDA in accordance with institutional policy.

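### The only automatic study suspension rule ends 28 days after the first IFN-gamma dose, so it covers little of the IFN-gamma plus DLI phase

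*Protocol*

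**What the plan says.** Section 8.4.1 is the one suspension criterion: "The study will be suspended if there is any death within four weeks after the first dose of" IFN-gamma, provided the treating physician, site investigator or study investigator judges it probably or definitely due to IFN-gamma. Everyone on IFN-gamma then stops injecting, and IRB review follows. Section 8.4.2 has the principal investigator consult the IRB and "make the decision to resume or close the study for any SAEs that meet the criteria for pausing the study", but it adds no further criterion.

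The cohort 2 timetable is as follows.

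- Section 6.5.2.4 puts the visit that ends stage 1 at "Day +7 (-3 days to +5 days) after the first dose of" IFN-gamma and adds: "If DLI is available, the first dose of DLI will be infused within two weeks from this visit".
- Section 6.3.2 gives a wider range for the same decision point ("window: - 3 days to + 7 days").
- Section 6.4.2.2 spaces the infusions: "A minimum of four weeks after the first dose of DLI, the subject will receive the second DLI". The same minimum gap applies before the third.
- Section 6.4.2.2 also says that IFN-gamma "will be continued once weekly until four weeks of the last dose of DLI or 12 weeks after the first dose of" IFN-gamma, whichever is later.

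In cohort 1, visit 4 (section 6.5.1.5) falls on day 28, plus or minus 5 days, and the first DLI follows within two weeks. Section 8.1.1 makes adverse events of IFN-gamma "in relapsed patients after alloSCT with concurrent use of donor lymphocyte infusion, per CTCAE v5.0" a primary safety endpoint.

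**The concern.** Section 2.2 names GVHD as the main safety concern, and section 11 says that IFN-gamma might induce it, above all when given with DLI. T-cell doses also rise over time (Table 3), from 5 x 10^6/kg at the first infusion to as much as 1 x 10^8/kg (sibling) or 5 x 10^7/kg (unrelated) at the third. The suspension window is counted from the first IFN-gamma dose and takes no account of when DLI starts.

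Four weeks equals the monotherapy stage of cohort 1. Cohort 2 shortens that stage to one week, which moves most of the exposure into the combination phase, yet the window is unchanged. Suppose a cohort 2 subject dies on day 40, five days after a nominal second DLI, and the death is judged probably due to IFN-gamma. As written, the study would not be suspended. Other subjects, who inject at home, would stop only if someone with authority chose to act.

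**Working it through.** The plan gives no operating figure for this rule, so there is nothing to reproduce. The check is calendar arithmetic, with day 0 the first IFN-gamma dose.

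**Inputs**
- Window: 28 days (8.4.1).
- First DLI, cohort 2: nominally day 7. Earliest is 7 - 3 = day 4. Latest is 7 + 5 + 14 = day 26 (6.5.2.4), or 7 + 7 + 14 = day 28 with the range in 6.3.2.
- First DLI, cohort 1: nominally day 28. Earliest is 28 - 5 = day 23. Latest is 28 + 5 + 14 = day 47 (6.5.1.5).
- Last IFN-gamma day: 84, or four weeks after the last DLI if later (6.4.2.1, 6.4.2.2).

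**Formula**
Covered days = max(0, 28 - day of first DLI). Phase length = last IFN-gamma day - day of first DLI.

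| Cohort and first DLI | Last IFN-gamma day | Covered / phase | Share |
|---|---|---|---|
| 2, nominal day 7 | 84 | 21 / 77 | 27% |
| 2, earliest day 4 | 84 | 24 / 80 | 30% |
| 2, day 26 | 84 | 2 / 58 | 3% |
| 2, day 28 (6.3.2 range) | 84 | 0 / 56 | 0% |
| 2, three DLIs on days 7, 35, 63 | 63 + 28 = 91 | 21 / 84 | 25% |
| 1, nominal day 28 | 84 | 0 / 56 | 0% |
| 1, earliest day 23 | 84 | 5 / 61 | 8% |
| 1, day 47 | 84 | 0 / 37 | 0% |

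The dose-reduction step in 6.3.2 can delay the first DLI further, which can only lower coverage.

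**Later infusions.** In cohort 2 the second DLI cannot come before 4 + 28 = day 32, nor the third before 4 + 56 = day 60. In cohort 1 the second cannot come before 23 + 28 = day 51. All fall after day 28, so no day after a second or third DLI is ever covered.

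**Added chance of a pause if the window is extended.** The protocol gives no risk of a qualifying death after day 28, so assume p per patient and use 1 - (1 - p)^n. Section 8.2.1 gives three to six patients for cohort 2.

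| p (assumed) | n = 3 | n = 6 |
|---|---|---|
| 1% | 3% | 6% |
| 2% | 6% | 11% |
| 5% | 14% | 26% |

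**The case against.** The rule is clear and contradicts nothing. In cohort 1 its length matches the monotherapy stage, the period in which a death can be ascribed to IFN-gamma without DLI confusing the picture. That explains its origin, but it does not fit cohort 2.

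A reader might infer that a death after day 28 goes unnoticed. The documents do not support this.

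- Section 9.3 sends every serious adverse event to the investigator-sponsor within 24 hours or one business day.
- Section 9.4 takes fatal, associated and unexpected events to the IRB within 24 hours, and other reportable events within 10 days.
- Sections 6.4, 6.6.1.1 and 6.7 withhold DLI, or reduce or stop IFN-gamma, in a patient with GVHD.
- Section 13 lets the disease-center DSMB and the DSMC suspend accrual. Its wording plausibly reaches study treatment too, so it should not be read as limited to accrual.

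A reader might also infer that fatal GVHD escapes reporting, because 9.2.3 lists acute GVHD as expected and 9.4 exempts expected events. Some ambiguity remains, but 9.2.3 states no severity, 9.1 treats an event as unexpected if its severity was not specified, and 9.4 separately requires serious events to be reported.

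Nor does 8.4.1 demand that IFN-gamma be the sole cause. It simply does not say whether a death attributed jointly to IFN-gamma and DLI counts.

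The fair objection on size is that days are not risk. IFN-gamma drops to once weekly at week 8 in cohort 2 (6.4.2.2), so the uncovered days include lower exposure. Even over the three-times-weekly part, nominal coverage is (28 - 7)/(56 - 7) = 21/49 = 43%, taking the taper from 6.4.2.2 (6.5.2.5 places it earlier).

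The objection on cost also stands. A pause stops injections for everyone until the IRB responds, and 6.7 withdraws a subject from study treatment after six doses not given. At three doses a week that is 6/3 = 2 weeks.

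**Conclusion.** The point holds as a gap between automatic and discretionary suspension. In cohort 2 the only automatic rule covers nominally 27% of the combined-treatment days and at most 30%, with nothing after a second or third DLI. In cohort 1 the figures are 0% and at most 8%, but these matter less now, since the synopsis describes monotherapy safety there as confirmed.

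The percentages assume a full IFN-gamma course of at least 12 weeks, with DLI given inside the stated visit windows. They are shares of calendar time and should not be read as shares of risk. The pause probabilities rest wholly on assumed death risks.

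A reader might conclude that the safety monitoring is inadequate or the trial unsound. The prompt reporting, the patient-level GVHD rules, the standing authority of the monitoring bodies and the small cohort do not support that. It is worth fixing because the change is small and falls where the protocol itself expects the greatest hazard.

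**What to change.** Amend 8.4.1 along these lines: enrolment and all IFN-gamma injections are suspended on any death, from a subject's first IFN-gamma dose through that subject's visit 8 (28 days after the last IFN-gamma dose), that is judged probably or definitely due to IFN-gamma, alone or in combination with DLI. This follows closely the period over which 6.5 and 9.5 already collect adverse events.

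Add to 6.7 that doses missed because of a study-level pause do not count toward the six-missed-dose withdrawal rule. Without this, a pause of about two weeks could remove patients under treatment for relapse. The same problem exists under the present rule.

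The cost is a short amendment and a somewhat higher chance of a temporary pause that interrupts injections for all subjects until IRB review. Deaths attributed to disease progression or to DLI alone stay outside the rule, so the high background mortality would not trigger it. The amended rule still counts deaths only and adds no trigger for non-fatal severe GVHD, which remains with the patient-level rules and the monitoring bodies.

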### 8.4.2 Criteria for study resumption after a safety pause

The IFN- $\gamma$  injection and enrollments of new subjects would resume only if a review of the adverse events that caused the pause resulted in an IRB recommendation to permit further study injections and study enrollments.

The Principal Investigator will consult with the IRB to conduct the review and make the decision to resume or close the study for any SAEs that meet the criteria for pausing the study. As part of the pause review, the reviewers will also advise on whether the study needs to be paused again for any subsequent adverse events of the same type. When indicated, safety data reports and changes in study status will be submitted to the IRB and FDA in accordance with institutional policy.

## 9. ADVERSE EVENTS: LIST AND REPORTING REQUIREMENTS

### 9.1 Definitions

Adverse event: Any untoward medical occurrence associated with the use of the drug in humans, whether or not considered drug-related.

Suspected adverse reaction: Any adverse event for which there is a reasonable possibility that the drug caused the adverse event (considered "possibly related"). For the purposes of safety reporting, "reasonable possibility" means there is evidence to suggest a causal relationship between the drug and the adverse event. Suspected adverse reaction implies a lesser degree of certainty about causality than adverse reaction, which means any adverse event caused by a drug.

Serious Adverse Event: Any untoward medical occurrence associated with the use of a drug in humans, whether or not considered drug related. Serious adverse events are defined by federal regulations and include events which:

- Are fatal or life threatening
- Result in significant or persistent disability
- Require or prolong inpatient hospitalization
- Result in a congenital anomaly or neoplasm
- Result from an overdose

- Are other conditions which in the judgment of the PI represents a significant hazard

Life-threatening, suspected adverse reaction: A suspected adverse reaction is considered “life-threatening” if, in the view of the Investigator (i.e., the study site principal investigator), its occurrence places the patient or research subject at immediate risk of death. It does not include a suspected adverse reaction that had it occurred in a more severe form, might have caused death.

Unexpected, suspected adverse reaction: A suspected adverse reaction is considered “unexpected” if it is not listed in the general investigational plan or clinical protocol, or is not listed at the specificity or severity that has been previously observed and/or specified. If an investigator brochure is not required or available, suspected adverse reaction is not consistent with the risk information described in the general investigational plan or elsewhere in the current application, as amended. “Unexpected,” as used in this definition, also refers to adverse events or suspected adverse reactions that are mentioned in the investigator brochure as occurring with a class of drugs or as anticipated from the pharmacological properties of the drug, but are not specifically mentioned as occurring with the particular drug under investigation. Any clinically important increase in the rate of a serious suspected adverse reaction over that listed in the protocol or investigator brochure can also be considered unexpected. An aggregate analysis of specific events observed in a clinical trial (such as known consequences of the underlying disease or condition under investigation or other events that commonly occur in the study population independent of drug therapy) that indicates those events occur more frequently in the drug treatment group than in a concurrent or historical control group.

All observed or volunteered adverse events (serious or non-serious), regardless of a study group or suspected causal relationship to the study drug(s) will be recorded in the subjects’ case histories. For all adverse events, sufficient information will be pursued and/or obtained so as to permit 1) an adequate determination of the outcome of the event (i.e., whether the event should be classified as a serious adverse event) and 2) an assessment of the causal relationship between the adverse event and the study drug(s). All toxicities encountered during the study will be evaluated on an ongoing basis, according to the NCI Common Toxicity Criteria version 5.0.

## **9.2 Expected Adverse Events**

### **9.2.1 Related to phlebotomy, bone marrow examination, and research sample collection**

Grade 1-2 of the following signs and symptoms are expected in phlebotomy and research sample collection:

1. Minor bleeding and bruising at the site of biospecimen collection
2. Minor infection at the site of biospecimen collection
3. Scar at the site of biospecimen collection
4. Pain or itching at the site of biospecimen collection
5. Light-headedness, fainting, and nausea due to vasovagal reactions

### **9.2.2 Related to ACTIMMUNE® (interferon gamma-1b)**

The expected adverse events related to ACTIMMUNE® (interferon gamma-1b) are

described in the prescribing information.

### 9.2.3 Related to donor lymphocyte infusion

The following symptoms and signs are expected adverse events associated with donor lymphocyte infusion.

- 1) Acute GVHD (up to 61 %)
- 2) Chronic GVHD
- 3) Bone marrow aplasia
- 4) Infusion reaction

### 9.2.4 Related to allogeneic stem cell transplantation

The following symptoms and signs are expected adverse events for the transplant recipient

- 1) Renal insufficiency
- 2) Hepatic insufficiency
- 3) Transient cardiac arrhythmias
- 4) Transient cardiac insufficiency
- 5) Pulmonary insufficiency
- 6) Neutropenia and its complications
- 7) Thrombocytopenia and its complications
- 8) Anemia and its complications
- 9) Treatable infections from bacteria, viruses, protozoa and fungi
- 10) Late effects of transplant regimens including chronic fatigue, cataracts, infertility, growth impairment, hypothyroidism, bone complications, and dental caries
- 11) Headache, insomnia, psychosis, mood changes, disorientation, seizures from metabolic imbalance
- 12) Nausea, vomiting, diarrhea, mucositis, weight loss, dry mouth, hiccoughs, constipation
- 13) Well-characterized drug reactions - allergic manifestations, "red man" syndrome, steroid effects
- 14) Well-characterized drug side effects from drugs used routinely in transplant recipients (e.g.; immunosuppressive drugs, antimicrobials)
- 15) Common side effects of antiemetics, analgesics, anti-inflammatory agent and known complications of steroid therapy
- 16) Complications from intravenous catheters, thrombotic occlusion, infection, local reactions, cardiac arrhythmia

